#### **Case control Analysis of Primary objective:**

All the subjects screened positive by ASHA are case here. The subjects who mental health are screen negative by ASHA, but screen positive by interviewer are kind of control in this study setup. Such subjects will be called as control.

A case control analysis will be performed to assess the difference in anxiety and depression score and mental health service utilization.

For this difference in anxiety and depression score for individual subjects will be computed from ASHA screen data and post intervention data. Further this difference in case and control will be statistically analyses by 2 independent sample t-test. Difference of difference in score between case and control along with p-value will be presented.

For health service utilization between cases and control, Count along with percent and Chi- square P-value will be presented.

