**Smart mental health Visit schedule and analysis for visit:**

The study will be reported in mainly 2 category:-

1. Baseline (As applicable, this will includes ASHA screening data available in in ASHA Screening 1 and ASHA follow up 1. OR Baseline data collected by study interviewers)
2. Post Intervention (collected by study interviewers)

All the subject at post intervention are screen positive subjects. They were screened positive either at Baseline by study interviewers or at Intervention visits (ASHA screening 1 and ASHA follow-up 1) by ASHA. All the screen positive subjects were followed by ASHAs which is available in the ASHA follow up data.

Unless otherwise stated, the summary tables will be presented under 2 category:-

1. Baseline
2. Post Intervention

The difference between Baseline and Post Intervention will provide effect of intervention.

Apart from the Post Intervention data, post stigma data was also collected. At the time of creating derived data for post Intervention, both data (Post Intervention and post stigma) are appended together and created a single data set. A flag variable containing record ("Post Intervention" & "post stigma") was created was created in derived data set to identify such records.

Unless otherwise stated, all the analysis will be presented for all the subject who are screen positive by ASHA.

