#### **Secondary Analysis Depression and Anxiety Score:**

The subjects are classified as screen positive if he/she fulfil either one of below mentioned three category:-

1. Depression Sore  $\geq 10$
2. Anxiety Score  $\geq 10$
3. Suicidal tendency Score  $\geq 1$

The depression and anxiety will be categorized as Normal if their total score is in between 0-

4. The score in between 5-9 will be classify as Mild. The score in between 10-14 will be classify as moderated. The score of 15 or greater will be treated as severe.

The Anxiety and Depression score will be categorized by their severity. The count and percentage for depression and Anxiety at baseline and post baseline will be presented by severity. A separate table will be presented for depression score  $\geq 10$  and anxiety score  $\geq 10$  at baseline and post intervention.

A separated table will be provides for the only screen positive subjects with the count and percentage of the symptoms which lead them to be screen positive.

The summary statistics (N, Mean, STD, Min and Max) for anxiety and depression score by visit will be presented. The difference in score between baseline and post intervention will be summarized in similar fashion. The mean difference in score between baseline and post intervention will be statistically analyzed by paired t-test. The p-value from the analysis will be presented in same table.

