|            |         | Mean (SD)  | xx.x (xx.xx) | xx.x (xx.xx)      | xx.x (xx.xx) |                        |
|            |         | Median     | xx.x         | xx.x              | xx.x         |                        |
|            |         | Min, Max   | xx; xx       | xx; xx            | xx; xx       |                        |
| Depression | Cases   | N          | xxxxx        | xxxxx             | xxxxx        | 0.xxxx                 |
|            |         | Mean (SD)  | xx.x (xx.xx) | xx.x (xx.xx)      | xx.x (xx.xx) |                        |
|            |         | Median     | xx.x         | xx.x              | xx.x         |                        |
|            |         | Min, Max   | xx; xx       | xx; xx            | xx; xx       |                        |
|            | Control | N          | xxxxx        | xxxxx             | xxxxx        |                        |
|            |         | Mean (SD)  | xx.x (xx.xx) | xx.x (xx.xx)      | xx.x (xx.xx) |                        |
|            |         | Median     | xx.x         | xx.x              | xx.x         |                        |
|            |         | Min, Max   | xx; xx       | xx; xx            | xx; xx       |                        |

\* Case: The subjects who are screen positive by ASHA.

\*\* Control: The subjects who are screened negative by ASHA but positive by study interviewer.

P-Value is calculated based chi-square independent sample test of proportion.

Table 16b: Case control analysis for health service utilization

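### Cases and controls in the case-control analysis are selected by different screening rules, so the unadjusted contrast is biased with no intervention effect: towards cases on the ASHA baseline, towards controls on an interviewer baseline

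*SAP*

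**What the plan says.** In the SAP section on the case-control analysis of the primary objective, cases are defined by one condition: "All the subjects screened positive by ASHA are case here". Nothing is required of the interviewer's result. Controls are defined by two: "The subjects who mental health are screen negative by ASHA, but screen positive by interviewer are kind of control in this study setup". The footnotes to Tables 16a and 16b repeat the control rule ("The subjects who are screened negative by ASHA but positive by study interviewer"), so it is not a slip of wording.

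The change score has a stated source for both groups: "For this difference in anxiety and depression score for individual subjects will be computed from ASHA screen data and post intervention data". The test is then fixed: "Further this difference in case and control will be statistically analyses by 2 independent sample t-test". Service use gets a chi-square test. Neither the section nor the two table shells names a matching variable, a covariate or a caveat about comparability.

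Two other places bear on this. The section on depression and anxiety scores makes a person screen-positive on any one of three criteria: depression at least 10, anxiety at least 10, or suicidal tendency at least 1. The title of Table 16a limits the analysis to a score of at least 10 at the start of the intervention but, unlike the title of Table 8b, does not say whose score.

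**The concern.** A t-test on change reads as evidence about the intervention only if the two groups would otherwise have moved alike. Here they would not. Cases are chosen for a positive ASHA screen. Controls are chosen for a negative ASHA screen together with a positive interviewer screen, which picks out people in whom one of the two results is likely to be off. Whichever rater supplies the baseline, that baseline has been selected differently in the two groups, so it drifts towards the mean by different amounts.

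This is the SAP's only between-group comparison on its primary objective. The other tests of these outcomes (McNemar and paired t-tests) compare before with after. A small p-value here would naturally be taken as controlled evidence, although the selection rule alone can produce it. The service-use comparison in Table 16b has a related problem: the groups are picked by different severity rules, and no score restriction or adjustment applies.

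**Working it through.** **Inputs from the SAP.** Case and control definitions, the ASHA baseline for change, the unadjusted tests, the cut-off of 10 and the three-criterion screening rule. The SAP states no sample size, mean, SD or reliability, so there is no figure of its own to reproduce.

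**Assumed inputs.** Each score has mean 5 and SD 5. The interviewer baseline (I), ASHA (A) and post-intervention interviewer (P) scores on a scale are exchangeable, with pairwise correlation r = 0.3, 0.5 or 0.7. There is no true change and no intervention effect.

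**Step 1: hand check, one scale, r = 0.5, normal scores.** Two standard results apply.
- Given A only: E[P] = E[I] = 5 + r(A - 5).
- Given A and I: E[P] = 5 + [r/(1 + r)] × [(A - 5) + (I - 5)], and r/(1 + r) = 1/3.

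Take three illustrative people:
- Case with A = 12, interviewer result not selected on: E[P] = E[I] = 5 + 0.5 × 7 = 8.50. Change is -3.50 from the ASHA score and 0 from the interviewer score.
- Control with A = 6, I = 12: E[P] = 5 + (1 + 7)/3 = 7.67. Change is +1.67 from the ASHA score and -4.33 from the interviewer score.
- Case with A = 12, I = 12: E[P] = 5 + (7 + 7)/3 = 9.67. Change from the interviewer score is -2.33.

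Case minus control, true value 0:
- ASHA baseline: -3.50 - 1.67 = -5.17 (favours the case).
- Interviewer baseline: 0 - (-4.33) = +4.33 (favours the control).
- Interviewer baseline, both interviewer-high: -2.33 - (-4.33) = +2.00.

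**Step 2: simulation under the SAP's three-criterion rule.** This adds a depression-anxiety true-score correlation of 0.6 or 0.8, a suicide item positive in about 6%, and scores clipped to 0-27 (the ceiling is also an assumption). There are 2,000,000 subjects per scenario. The table gives the false difference in depression change, case minus control; a negative value favours cases.

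| Analysis | r = 0.3 | r = 0.5 | r = 0.7 |
|---|---|---|---|
| ASHA baseline, SAP groups | -3.3 | -2.6 | -1.8 |
| Interviewer baseline, SAP groups | +2.2 | +1.8 | +1.3 |

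With an interviewer baseline and interviewer score at least 10 in both groups, the difference is +1.2 to +1.9 across scenarios.

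**Step 3: can the Table 16a restriction rescue it?** Read on ASHA data, no control qualifies, because an ASHA-negative person scores below 10 on both scales by definition. Read on interviewer data, the last result in Step 2 applies and bias remains. Table 16b carries no such restriction.

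**Step 4: does adjustment work?** In the same no-effect setting, with cases also required to be interviewer-positive:
- Interviewer baseline plus the ASHA score of the analysed scale: 0.5 to 1.0 points remain.
- Both scales and the suicide item from both raters: -0.1 to 0.0 remains.

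**Sensitivity.** A different one-scale error model (true mean 4-5, true SD 3-4, reliability 0.5-0.9) gave the same signs throughout: -1.4 to -6.2 on the ASHA baseline, +1.3 to +4.9 on the interviewer baseline, and +0.9 to +1.9 with interviewer score at least 10 in both groups.

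**The case against.** Four points can be made for the plan or against a stronger criticism.

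- **Direction.** A reader might infer that the analysis as specified would show apparent harm. It would not. The SAP takes change from ASHA data, and on that baseline the bias favours cases. Apparent harm arises only if the baseline is switched to the interviewer and nothing else is altered.
- **Size.** A one-scale simulation with the same mean, SD and correlations gives larger figures: -6.9/-5.5/-3.9 on the ASHA baseline and +5.6/+4.5/+3.2 on the interviewer baseline. These overstate the case, because the SAP lets a person qualify on either scale or on the suicide item. Many people are then not selected on the scale being analysed. The smaller three-criterion figures are the ones to use.
- **Remedy.** It is tempting to adjust for one ASHA score as the variable that assigns the group. No single score does so under the SAP's rule, and Step 4 shows that this leaves bias behind.
- **Weight.** The visit-schedule section places the intervention effect in the baseline to post-intervention difference, and the SAP itself hedges in calling these people controls. That is fair and lowers the severity. The section is nonetheless titled as an analysis of the primary objective and yields a p-value without a caveat.

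The visit-schedule section also says that ASHAs followed all screen-positive subjects, and that those at post-intervention became so by either route ("They were screened positive either at Baseline by study interviewers or at Intervention visits"). The controls may therefore not be unexposed, and no regression settles that.

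**Conclusion.** The point holds, as something that should be fixed. The asymmetric selection and the unadjusted tests are stated in the text, and the bias follows from them. With no intervention effect, the specified ASHA baseline gives a false advantage to cases of about 3.3/2.6/1.8 depression points at correlation 0.3/0.5/0.7. An interviewer baseline gives about 2.2/1.8/1.3 points the other way. Aligning the interviewer threshold at 10 in both groups leaves 1.2 to 1.9 points in favour of controls. The signs held in every scenario run. The sizes rest on assumed means, SDs, correlations and suicide-item frequency, and should be read as orders of magnitude. No size was computed for service use; there the point is that groups differing in severity by construction are compared without adjustment.

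**What to change.** In the case-control section and Tables 16a and 16b:

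1. For this contrast only, define cases as ASHA-positive and interviewer-positive at baseline, so that both groups meet the same interviewer criterion.
2. Replace the t-test on change with a linear model of the post-intervention interviewer score on group. Adjust for everything that determines screen status (depression score, anxiety score and suicidal-tendency item, each from both the interviewer baseline and the ASHA screen), plus age and sex.
3. Use a logistic model with the same covariates for post-intervention service use.
4. Show the unadjusted contrasts as descriptive only. State that the adjusted estimate depends on the modelled form across the ASHA cut-off, where the groups do not overlap. State also that, since all screen-positives are said to have been followed by ASHAs, a difference is not a clean intervention effect.

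The cost is SAP wording and one regression per outcome, using the two scores and the suicide item that both screens rely on. Interviewer-negative cases leave this comparison. The interval widens because group status is closely tied to the ASHA variables. In a one-scale run the variance of the group coefficient rose roughly 2.5-fold, making the interval about 1.6 times as wide (√2.5 = 1.58).

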**Data selection criteria for Analysis:**

Unless otherwise stated, for baseline we have to use ASHA screening (ASHA screening 1 and ASHA follow-up 1) data. At post intervention we have to use Post intervention data collected by study interviewers linked with patient ID of ASHA screen positive data.

For certain tables the information at baseline may not be collected by ASHA during their screening. For all such instance, Baseline data collected by study interviewers will be used linked with patient ID of ASHA screen positive data.

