| Did you take medicines as prescribed by the primary care doctor on a regular basis? | xx(xx.xx)                |

*N=Total no. of patients in Baseline; n=No. of patients in particular category*

Table 15: Summary of for Utilization of Health Services for Screen Positive subjects

| Screen Positive | Health Service used ** | Baseline
(N=xxxxx)
n (%) | Post Intervention
(N=xxxxx)
n (%) | P-value |
|-----------------|------------------------|--------------------------------|-----------------------------------------|---------|
| By ASHA         | Yes                    | xxx (xx.xx)                    | xxx (xx.xx)                             | 0.xxxx  |
|                 | No                     | xxx (xx.xx)                    | xxx (xx.xx)                             |         |
| By Interviewer* | No                     | xxx (xx.xx)                    | xxx (xx.xx)                             | 0.xxxx  |
|                 | Yes                    | xxx (xx.xx)                    | xxx (xx.xx)                             |         |

\* This includes only those patients who were screen positive by Study Interviewer but not by ASHA.

\*\* Health Service used: At baseline: Response from the question "Did you get treated for that mental disorder?"

At Post Intervention: Response from the question "Did you get treated for your mental health condition as indicated by ASHA/Interviewer?"

P-Value is calculated based on Mc-nimar test for matched pair test of proportion.

Table 16a: Case control analysis of Change in Depression/Anxiety Score from Baseline to Post Intervention for those who had a score  $\geq 10$  at the beginning of the intervention.

| Category   | Type    | Statistics | Baseline     | Post Intervention | Change       | P-Value for difference |
|------------|---------|------------|--------------|-------------------|--------------|------------------------|
| Anxiety    | Cases   | N          | xxxxx        | xxxxx             | xxxxx        | 0.xxxx                 |
|            |         | Mean (SD)  | xx.x (xx.xx) | xx.x (xx.xx)      | xx.x (xx.xx) |                        |
|            |         | Median     | xx.x         | xx.x              | xx.x         |                        |
|            |         | Min, Max   | xx; xx       | xx; xx            | xx; xx       |                        |
|            | Control | N          | xxxxx        | xxxxx             | xxxxx        |                        |

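### The case-control score comparison takes change from the ASHA score that assigns the groups: Table 16a has no eligible controls on that baseline, and other readings that keep it bias the result towards benefit

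*SAP*

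**What the plan says.** Four parts of the SAP bear on this comparison.

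- **Groups.** The section on the case control analysis of the primary objective says "All the subjects screened positive by ASHA are case here". The footnote to Table 16a defines the other group: "Control: The subjects who are screened negative by ASHA but positive by study interviewer".
- **Change score.** The same section says "For this difference in anxiety and depression score for individual subjects will be computed from ASHA screen data and post intervention data". The changes in the two groups are then compared by an independent two-sample t-test.
- **Screening rule.** Under Secondary Analysis, "The subjects are classified as screen positive if he/she fulfil either one of below mentioned three category". The three routes are a depression score of at least 10, an anxiety score of at least 10, or a suicide score of at least 1.
- **Population of Table 16a.** The title reads "Case control analysis of Change in Depression/Anxiety Score from Baseline to Post Intervention for those who had a score" and goes on to require at least 10 at the beginning of the intervention. It does not say whose score. The title of Table 8b, which carries the same cut-off, names the ASHAs.

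The section on data selection sets the general rule: "Unless otherwise stated, for baseline we have to use ASHA screening (ASHA screening 1 and ASHA follow-up 1) data". Its exception begins "For certain tables the information at baseline may not be collected by ASHA during their screening", and only then is the interviewer baseline used. For follow-up, "At post intervention we have to use Post intervention data collected by study interviewers linked with patient ID of ASHA screen positive data".

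The footnote under Table 16a attributes the p-value to a chi-square test of proportions.

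**The concern.** The ASHA score does two jobs. It decides who is a case or a control, and it is the value subtracted from the follow-up score. Controls are selected to be low on it and cases are largely selected to be high on it. Requiring a high starting score on the same measure then excludes every control.

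If the requirement is relaxed, chance movement away from the selected values goes in opposite directions in the two groups, and the t-test cannot separate it from an effect. Rater and time point also change together, from ASHA at the start to interviewer at follow-up.

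This is the plan's only between-group test of the anxiety and depression scores. As written, the analyst would have to choose an unstated baseline source, possibly after seeing the data.

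**Working it through.** The SAP gives no effect size, SD, correlation or sample size for this comparison, so there is no figure to reproduce.

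**Step 1: the definitions (no assumptions needed).**

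- Screen positive = depression ≥10, or anxiety ≥10, or suicide score ≥1.
- So ASHA negative means ASHA depression ≤9, ASHA anxiety ≤9 and suicide score 0.
- A control is ASHA negative, so both its ASHA scores are ≤9.
- Table 16a requires a score ≥10 at the start. On the ASHA score, eligible controls = 0.

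The exception in the data selection rule does not help, because ASHAs did collect both scores. The visit schedule section allows the interviewer baseline where applicable, and Tables 7a and 8a have interviewer rows. Nothing assigns that score to controls here.

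**Step 2: why change from ASHA is biased.** Suppose there is no effect, three exchangeable measurements (ASHA, interviewer baseline, follow-up) with mean m and correlation r, and linear regression to the mean. Then:

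- E(post | ASHA = a) = m + r(a − m)
- E(post | ASHA = a, interviewer = b) = m + [r/(1 + r)] × [(a − m) + (b − m)]

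Take m = 3 and r = 0.5 as an illustration. The case has an ASHA score of 10 (the cut-off). The control has an ASHA score of 5 (bottom of the mild band) and an interviewer score of 10.

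- Case: 3 + 0.5 × 7 = 6.5, so change from ASHA = −3.5.
- Control: 3 + (1/3) × (2 + 7) = 6.0, so change from ASHA = +1.0.
- Difference of changes: −3.5 − 1.0 = **−4.5** with no effect.
- Mixed sources (ASHA for the case, interviewer for the control): control change = 6.0 − 10 = −4.0, so the difference = −3.5 + 4.0 = **+0.5**.
- Interviewer baseline in both, case also at 10 on it: 3 + (1/3) × (7 + 7) = 7.67, change −2.33, difference = −2.33 + 4.0 = **+1.67**.
- That remainder is (1/3) × (10 − 5) = 1.67, which is the ASHA term. Adjusting for the ASHA score as well as the interviewer score leaves **0**.

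**Step 3: simulation with no effect and no time trend.** Twelve scenarios of 1,000,000 people each applied the full screening rule. Assumptions not in the SAP:

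- score mean 3 to 6, SD 4 to 5
- ceilings 27 (depression) and 21 (anxiety)
- depression-anxiety correlation 0.6
- suicide item positive in 0 to 2%, five times higher if depression ≥10.

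Depression, difference of changes, change taken from ASHA, no ≥10 filter:

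| Correlation between measurements | Case minus control |
|---|---|
| 0.3 | −4.2 to −5.0 |
| 0.5 | −3.3 to −4.0 |
| 0.7 | −2.3 to −2.9 |
| 0.9 | −1.0 to −1.4 |

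The chance of a falsely significant benefit (two-sided 0.05) was 82% to 100% with 50 per group and at least 98% with 100 per group. With the ≥10 filter read as the interviewer's score for controls and change still taken from ASHA, the difference was −1.7 to −6.9.

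A separate simulation under the depression-or-anxiety rule (mean 3, SD 4, correlation 0.43 to 0.93) gave:

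- ASHA baseline in both groups, no filter: about −6.0 to −1.5.
- ASHA baseline for cases, interviewer baseline for controls: about +0.6 to +1.3.

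Analysing interviewer baseline and post scores by ANCOVA on both the interviewer and the ASHA score brought the null estimate to about −0.35 to +0.12. Simple change from the interviewer baseline in both groups left +0.9 to +1.6 in the twelve scenarios, so changing the baseline alone is not enough.

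**The case against.** The strongest objection is that the empty control arm rests on one reading. Table 16a does not name the screener, whereas Table 8b does, so the authors may have meant each group's criterion to come from whoever screened it positive. That would fill the Control rows. Taking each group's baseline from the same source would also give the smallest residual bias of the unadjusted options, because both groups then start from values selected to be high. This stands as a guess at intent. It contradicts the sentence that computes change from ASHA data, and it compares different raters at baseline. Any systematic ASHA-interviewer difference would come on top of the residual.

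A reader might also infer three stronger points that the SAP does not support.

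- **That Table 16a has no controls on any reading.** This follows only if the criterion is the ASHA score.
- **That the false benefit is necessarily large.** A simulation with one score as the only route to positivity gives −9.4 to −5.1 points. The SAP's rule admits cases through the other scale or the suicide item, so many cases are below 10 on a given scale and fall less. At a correlation of 0.9 the bias is about 1 point. The no-filter figures also apply only if the filter in Table 16a is dropped.
- **That this is the only between-group analysis of the primary objective.** That objective also covers service use, which Table 16b compares separately between cases and controls.

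**Conclusion.** The point holds. On the baseline the SAP states, the Control rows of Table 16a are empty by definition. On either alternative that keeps change from ASHA (the interviewer's score as the criterion for controls, or no criterion), the comparison is biased towards benefit. The direction was the same in every scenario examined.

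The size is not determined by the SAP. About −6.0 to −1.5 depression points without the filter is the working range for mean 3, SD 4 and correlation 0.43 to 0.93; the twelve scenarios with other assumptions gave −5.0 to −1.0. All of these figures assume no systematic rater difference and no time trend.

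Because this is the only between-group test of the scores, the passages must be reconciled before analysis. The within-group paired tests and the service-use comparison are separate analyses and do not replace it.

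**What to change.** 1. In the case control section and in Table 16a, take the baseline score and the ≥10 criterion from the study-interviewer baseline in both groups, and name that source in the table title.
2. Replace the t-test on change with ANCOVA of the interviewer's post-intervention score on group, interviewer baseline score and ASHA screening score. Report the adjusted difference with its 95% CI.
3. State that the comparison is non-randomised and relies on linearity around the ASHA cut-off, since the ASHA score largely determines group.
4. Replace the chi-square footnote under Table 16a. A test of proportions does not fit mean changes and contradicts the t-test in the text.

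The cost is SAP wording, one model and some subjects. Cases with no linked interviewer baseline, or below 10 on it, leave the table; in simulation about 20 to 50% of cases remain under the depression-or-anxiety rule. Controls positive only on the other scale leave that scale's comparison; about 53 to 59% remain for depression. The model does not address the suicide-item route to positivity. Other adjusted analyses could be defended, but the baseline source and the criterion have to be fixed in either case.
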